### Eligibility Criteria

Male and female smokers over the age of 18 years who have smoked more than 10 cigarettes per day during the past year and during the month before the screening visit are eligible to participate in the study. Smokers must also be prepared and motivated to quit smoking (score of 7 or higher on the visual analog scale of motivation). Smokers who have received pharmacological treatment for nicotine dependence (nicotine replacement therapy, varenicline, bupropion, or cytisinicline) within the previous 3 months are excluded from participating in the clinical trial.

In addition, exclusion criteria (Textbox 1) have been designed, taking into account the considerations of the drug label. All patients meeting all inclusion criteria and no exclusion criteria are consecutively invited to participate until the calculated sample size is obtained in each center.

Exclusion criteria for the study.Renal and/or hepatic insufficiency.Over 65 years of age (due to limited clinical experience).Hypersensitivity to the active substance or to any of the excipients.Unstable angina.Recent personal history of acute myocardial infarction or recent stroke (less than 8 weeks).Clinically relevant arrhythmias or uncontrolled hypertension.History of psychiatric illness with and without treatment (panic disorder, psychosis, bipolar disorder, and depression) within the last 12 months.History of alcohol or other drug abuse within the last 12 months.Use of tobacco products other than cigarettes, e-cigarettes, or marijuana in the past month and did not agree to abstain from using these products during study participation.Patients being treated with antituberculosis drugs.Patients being treated with drugs metabolized by CYP1A1 (cytochrome *P* 450 family 1, subfamily A, polypeptide 1) and CYP1A2 (cytochrome *P* 450 family 1, subfamily A, polypeptide 2), especially those with a narrow therapeutic margin (eg, theophylline, tacrine, clozapine, and ropinirole).Pregnant or breastfeeding smokers.Women on systemic hormonal contraceptives.

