### Specific Outcomes (Safety)

The impact of morbidity and mortality in each treatment arm will be evaluated, as well as the percentage of side effects reported by participants, comparing their prevalence in each group throughout the study (1 year). The percentage of adverse effects at 25, 50, and 75 days will also be determined in participants, comparing their prevalence in each group.

Furthermore, the prevalence and severity of side effects for each regimen will be compared throughout the study (1 year).

Finally, the results of cardiac, hepatic, and renal variables will be compared between each group as indicators of treatment safety in each group at 25, 50, and 75 days of treatment and throughout the entire study period (1 year).

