### Schedule of Participants

Table 3 and Figure 1 show the screening visit, follow-up visits (face-to-face and telephone), tests and quizzes to be carried out at each of the visits, and the interventions.

**Table 3 table3:** Visiting calendar. The screening visit, follow-up visits (face-to-face and telephone), tests and quizzes to be carried out at each of the visits, as well as the intervention.

Number, day, and type of visit		Visit 1 (day 1; in person)		Visit 2 (day 7; in person)		Visit 3 (day 14; telephone)		Visit 4 (day 21; in person)		Visit 5 (day 25; telephone)		Visit 6 (day 50; telephone)		Visit 7 (day 75; telephone)		Visit 8 (day 90; in person)		Visit 9 (day 120; in person)		Visit 10 (day 150; in person)		Visit 11 (week 24; in person)		Visit 12 (week 36; telephone)		Visit 13 (week 48; in person)		Visit 14 (week 52; in person)			

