Other qualities of the smoker, such as the degree of motivation and self-efficacy, will be evaluated by the Analogue Visual Scale. This scale numerically identifies a smoker’s level of motivation and self-efficacy to quit smoking. A score above 7 indicates high motivation and self-efficacy to quit smoking [27].

The EQ-5D scale will be used in this clinical trial to assess the quality of life of smokers and its changes during the smoking cessation process. This scale measures the health status of smokers using 5 dimensions, including mobility, self-care, activities of daily living, pain and discomfort, and anxiety and depression. Participants score from 0 to 100 in each domain [31].

The urge to smoke in this study will be analyzed using the Craving Rate Score. This scale assesses anxiety or intense desire to smoke at baseline and during follow-up. It is scored from 0 to 4 [32].

The additional tests that will be performed on smokers participating in this trial include electrocardiogram, carbon monoxide levels, complete blood count, and a biochemical profile that includes liver enzymes, electrolytes, and renal function tests. Co-oximetry allows for the objective identification of smoking status, as well as confirmation of abstinence at each participant visit. A participant is identified as a nonsmoker when their CO levels measured by co-oximetry are below 10 ppm (Textbox 2).

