Efficacy and safety variables of cytisinicline.To analyze the efficacy of cytisinicline we used the following variables:Continuous abstinence rate at six months of treatmentEfficacy of the maintained cytisinicline regimens (50 and 75 days) compared to the usual 25-day regimen calculated every 7 daysIntervention interval effectivenessAbstinence rate between days 25 and 50Abstinence rate between days 25 and 75Abstinence rate between days 25 and 6 months calculated every 7 daysAnalysis of withdrawal syndromeMNWS score at each visitVariation in MNWS score between visitsMean MNWS score at each visitCraving AnalysisSRC score at each visitChange in SRC score at each visitAverage SRC score at each visitTo analyze the safety of cytisinicline, we used the following variables:Number and percentage of self-reported adverse events at the baseline visitNumber and percentage of self-reported adverse events on days 7, 15, 25, 50, and 75Number and percentage of mild, moderate, or severe adverse events on days 7, 15, 25, 50, and 75Number and percentage of serious adverse events on days 7, 15, 25, 50, and 75Number and percentage of the following adverse events: nausea, vomiting, constipation, abdominal distension, abdominal pain, epigastric pain, nightmares, insomnia, parasomnias, headache, and dizzinessPercentage of patients with electrocardiographic abnormalities at the initial visitPercentage of patients with electrocardiographic alterations at 25, 50, and 75 daysPercentage of patients with electrocardiographic alterations at 25, 50, and 75 daysPercentage of patients with abnormal liver enzyme levels at the baseline visitPercentage of patients with abnormal liver enzyme levels at 25, 50, and 75 daysPercentage of patients with abnormal electrolyte levels at the baseline visitPercentage of patients with abnormal electrolyte levels at 25, 50, and 75 daysPercentage of patients with abnormal renal function at the baseline visitPercentage of patients with abnormal renal function at 25, 50, and 75 days

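### Textbox 2 compares ECG and laboratory abnormalities as crude percentages per visit; using each patient's baseline result would usually sharpen the comparison, at low priority

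*Protocol article*

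**What the plan says.** Textbox 2, under Data Collection Variables, introduces its safety list with the words "analyze the safety of cytisinicline, we used the following variables". For ECG, liver enzymes, electrolytes and renal function, the list gives the percentage of patients abnormal at the initial visit. A separate row gives the percentage abnormal on treatment, as in "patients with abnormal liver enzyme levels at 25, 50, and 75" days and "patients with electrocardiographic alterations at 25, 50, and 75" days. No row is restricted to patients normal at baseline, and none counts new or worsened findings. The same textbox does define change variables for the withdrawal and craving scores.

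Specific Outcomes (Safety) puts these tests to comparative use: the "results of cardiac, hepatic, and renal variables will be compared between each group as indicators of treatment safety". The Safety Analysis section names the chi-square test for qualitative variables, and logistic regression. Relative risk appears only in the Efficacy Analysis section.

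Textbox 1 excludes renal or hepatic insufficiency and clinically "relevant arrhythmias or uncontrolled" hypertension. It does not exclude a mildly raised enzyme, an abnormal electrolyte or a minor ECG finding as such.

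**The concern.** A percentage abnormal at a visit mixes two kinds of patient: those whose abnormality arose on treatment, and those who entered with it and still have it. Only the first kind bears on whether 50 or 75 days of cytisinicline causes new abnormalities. The second kind appears in all arms, raises the percentage in each, and adds variance.

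The trial hypothesises that longer treatment brings no more adverse events. In a safety comparison, lost sensitivity can be mistaken for reassurance. The baseline result that would remove much of this noise is already on the variable list.

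**Working it through.** **Inputs from the article.** It states no power or rate for these safety variables. Its only sample-size figure is for efficacy: 110 per arm, 402 in total. That reproduces. An overall three-group chi-square test with 30%, 45% and 50%, alpha 0.05 and 80% power needs 109 per arm. Then 110 × 1.21 = 133.1, rounded up to 134, and 134 × 3 = 402. For safety I use n = 134 per arm with no loss, and 134 × 0.79 = 106 with the 21% loss.

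**Assumed inputs.** Baseline prevalence b, share of baseline abnormalities persisting s, and new-onset risk q among patients normal at baseline.

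**Formulas.**
- Visit prevalence in an arm = s·b + (1 − b)·q, with n patients.
- New onset in an arm = q, with n(1 − b) patients.
- If s is the same in both arms, the s·b term cancels in the difference, so the risk difference is (1 − b)(q2 − q1).
- Power = Φ[(difference − 1.96·SE0) / SE1], with SE0 the pooled and SE1 the unpooled standard error, for a two-sided 5% test of one arm against another.

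**Worked example: b = 5%, s = 100%, q = 3% vs 10%, n = 106.**
- Visit prevalence: 0.05 + 0.95 × 0.03 = 7.85%, and 0.05 + 0.95 × 0.10 = 14.5%. The difference is 6.65 points, SE0 = 0.0433, SE1 = 0.0430. Power = Φ[(0.0665 − 0.0848)/0.0430] = 34%.
- New onset: 3% vs 10% with 106 × 0.95 = 100.7 per arm. SE0 = 0.0347, SE1 = 0.0344. Power = Φ[(0.0700 − 0.0681)/0.0344] = 52%.

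**Equal persistence in both arms, q = 3% vs 10% (power at n = 106 to 134).**

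| Baseline b | Visit prevalence, s = 100% | Visit prevalence, s = 30% | New onset | Risk difference by visit |
|---|---|---|---|---|
| 0% | 54-64% | 54-64% | 54-64% | 7.0 points |
| 2% | 44-53% | 50-60% | 54-64% | 6.86 points |
| 5% | 34-41% | 44-53% | 52-62% | 6.65 points |
| 10% | 24-29% | 36-44% | 50-60% | 6.3 points |

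The risk difference barely moves; the power loss comes mainly from the added variance. With a smaller effect, 3% vs 6% at b = 5%, power is about 11-12% (s = 100%) or 14-17% (s = 30%) by visit, against about 18-21% by new onset.

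**Unequal persistence: 30% on the standard regimen, higher on a longer one, q = 3% vs 10%.**
- b = 5%, 30% vs 50%: visit prevalence 53-63%, new onset 52-62%.
- b = 5%, 30% vs 60%: visit prevalence 57-67%, new onset 52-62%.
- b = 10%, 30% vs 60%: visit prevalence 61-71%, new onset 50-60%.

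Here the visit percentage picks up a drug effect in patients already abnormal, whom the new-onset analysis drops.

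**Timing.** Table 1 gives all arms the same dosing to day 25, so no regimen effect is expected at that time point. Table 3 has "Visit 5 (day 25; telephone") and "Visit 7 (day 75; telephone"), and day 50 is also by telephone. The in-person visits on either side are days 21 and 90.

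**The case against.** The strongest reply is that this is a journal article: treatment-emergent definitions, denominators and shift tables usually sit in the analysis plan, and a list of variables is not a prescribed analysis. Listing the baseline percentage leaves a baseline-referenced comparison open. This stands in part. The article does not rule out a better analysis. But it does fix the form of these safety variables, gives the withdrawal and craving scores change variables that the four tests lack, and says the cardiac, hepatic and renal results will be compared between arms.

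The second reply is that the power loss depends on persistence being equal across arms. This stands, as the unequal-persistence results show. New onset alone is not always the better comparison.

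A third reply is that a large baseline prevalence is unlikely given the exclusions. This also stands in part: the exclusions push it down but not to zero, and at 2% baseline with 30% persistence the loss is only 3 to 4 points.

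A reader might also infer stronger faults that the article does not support:
- Bias between arms: randomisation gives every arm the same expected baseline abnormalities.
- Double counting: each visit's percentage counts a patient once.
- A distorted risk ratio: no relative risk is planned for safety, so the test's power is what is affected.

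**Conclusion.** The point holds as an opportunity for better precision. The listed variables ignore baseline status, and if persistence is equal across arms the comparison loses power for new abnormalities whenever some baseline abnormalities persist. Under the assumed 3% vs 10% and full persistence, the loss is about 10 to 11 points at 2% baseline prevalence and 19 to 21 points at 5%. It is zero at 0% baseline and smaller when few abnormalities persist.

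The true size is unknown, because the article gives no baseline prevalence, persistence or new-onset rate. The figures also assume a two-sided 5% pairwise test. If longer treatment slows recovery of existing abnormalities, visit prevalence does as well or better. The trial was not sized for this comparison, and no scenario shown here reaches 80% power under either analysis. This is a low-priority improvement to a secondary objective.

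**What to change.** Use the baseline result that Textbox 2 already lists:

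1. Compare laboratory values, and numeric ECG measurements where recorded, between arms with adjustment for the baseline value in all patients. The data exist if the tests are done as described, since the article plans "a biochemical profile that includes liver enzymes, electrolytes, and renal function tests".
2. For each of the four test types, report new abnormalities among patients normal at baseline, with the risk difference and 95% CI.
3. Add a shift table from baseline to on-treatment status for each arm, so that persistence or worsening in patients already abnormal is visible. This matters most for categorical ECG findings, which step 1 cannot cover.
4. Keep the listed visit percentages as description.
5. Focus the comparison on time points after day 25, and state the visits at which the tests are really taken, since days 25, 50 and 75 are telephone contacts.

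The cost is revised variable wording, one shift table per test type and a baseline-adjusted model. No tests are needed beyond those listed. The downside is that patients abnormal or untested at baseline leave the new-onset denominator and must be reported separately.

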### Trial Monitoring

As this is a low-intervention trial, the monitoring and quality control processes of the generated database will be carried out by the principal investigators of each site or by a collaborating investigator of the team to whom this task is delegated.

### Pharmacovigilance

As this is a low-intervention study, the expected adverse events are those reflected in the drug label. The definition of adverse events, the classification of their severity, and the actions to be taken by the principal investigator and sponsor in the event of an adverse event are included in Multimedia Appendix 1. In all cases, the sponsor should promptly communicate to the investigators any important information that could adversely affect the safety of the participants or the conduct of the trial. The communication of such information should be concise and practical. The communication shall be in accordance with the criteria and procedure specified in the European Commission’s guidelines. The sponsor shall report to the Spanish Agency for Medicinal Products and Health Products all suspected serious and unexpected adverse reactions associated with the investigational medicinal products of which he/she has become aware. An adverse event is an undesirable experience that affects a patient during a clinical trial or study, whether or not it is considered to be related to the investigational product.

A serious adverse event is one that is life-threatening, causes persistent disability, or requires prolonged hospitalization of the patient. Apart from these, congenital anomalies and malignant neoplasms shall always be considered serious.

A nonserious adverse event is any adverse event that does not meet any of the above criteria.

An unexpected adverse event is an experience that is not described in the investigator’s manual (by nature, severity, or frequency occurred in the clinical trial).

### Statistical Analysis

#### Sample Size Determination

Based on clinical experience, it is estimated that the efficacy of cytisinicline prescribed in accordance with the data sheet is 30% (*P*^1^=.30), and that this efficacy will be greater if the maintenance regimen is extended over time. In this sense, it is hypothesized that the intermediate maintenance regimen could achieve an efficacy of 45% (*P*^2^=.40) and with the longest regimen, 50% sustained abstinence could be achieved (*P*^3^=.50). To obtain 80% power (pow=0.80) to detect differences at a 5% significance level (α=.05), 110 patients would need to be included in each arm. A loss rate of 21% is assumed, giving a final sample size of 402 patients (N=402).

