### Objectives

The overall objective of this study is to evaluate the efficacy, safety, and economic impact of 2 extended cytisinicline regimens (50 and 75 days duration) and compare them with the standard regimen (25 days).

The primary objective is to determine the efficacy of the maintained cytisinicline regimens (50 and 75 days) versus the standard 25-day regimen.

The secondary objectives are (1) to determine the percentage and number of adverse effects in each of the 3 treatment arms and (2) to analyze the economic impact of the maintained regimens versus the standard regimen in terms of cost-effectiveness and cost-utility.

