### Safety Analysis

The frequency and percentage of occurrence of adverse reactions shall be determined and categorized according to type/intensity. Calculate whether there are differences in each group compared to what is expected according to the product label.

To examine differences in the data between groups defined by the presence/absence of adverse events, the chi-square test will be applied for qualitative variables and the *t* test or the Mann-Whitney *U* test for quantitative variables. Finally, the causal relationship between safety, defined by the absence of adverse events, and treatment prolongation will be verified using multivariate logistic regression. To determine candidate variables, those with a statistical significance of *P*<.20 will be tested and included in a multivariate model.

All analyses will be performed with the statistical package SPSS (version 19.0; IBM Corp), and statistically significant values will be considered those whose *P* value is <.05.

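### The sample-size paragraph gives the 50-day rate as both 45% and .40 and does not say which comparison its 80% power is for; at 110 per arm, 50 versus 25 days has about 63% or 34%

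*Protocol article*

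**What the plan says.** Under Sample Size Determination, the article assumes that "the efficacy of cytisinicline prescribed in accordance with the data sheet is 30% (*P*^1^=.30"), that "the intermediate maintenance regimen could achieve an efficacy of 45% (*P*^2^=.40"), and that "with the longest regimen, 50% sustained abstinence could be achieved (*P*^3^=.50"). Words and symbol agree for the 25-day and 75-day arms. For the 50-day arm they do not.

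The power claim follows: "To obtain 80% power (pow=0.80) to detect differences" "at a 5% significance level (α=.05"), "110 patients would need to be included in each arm". A 21% loss allowance brings the total to 402, or 134 per arm. The paragraph does not say which test, which pair of arms, or how many sides the calculation used.

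Under Objectives: "The primary objective is to determine the efficacy of the maintained cytisinicline regimens (50 and 75 days) versus the standard 25-day regimen". Trial Design describes a superiority trial of maintenance therapy against the standard regimen. The only significance rule in the article closes the Safety Analysis section and covers all analyses: "statistically significant values will be considered those whose *P* value is <.05".

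**The concern.** Two things do not fit together. First, a design input has two values: the assumed 50-day benefit over 25 days is either 15 or 10 percentage points. Second, the stated power is for unspecified differences, while the primary objective asks two questions, one for each extended regimen against the standard one. A reader will naturally apply the 80% to both.

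This matters most for the 50-day arm. If that contrast is not significant, the result is likely to be read as a lack of effect in a trial described as having 80% power. On the article's own assumptions, the trial would miss a real 50-day benefit in about 37% of cases (rate 45%) or 66% (rate 40%). The Abstract presents the 50-day regimen as the one that should disturb adherence least, so discarding it wrongly would be a real loss.

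**Working it through.** **Inputs.** From Sample Size Determination: 25-day rate .30; 50-day rate .45 or .40; 75-day rate .50; power .80; alpha .05; 110 per arm; loss 21%; total 402. Two-sided testing is my assumption, and one-sided results are shown as well.

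**Step 1. Reproduce the 110.** Two routes lead to it.

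*(a) Global chi-square across three arms, 2 df.* With n per arm, the noncentrality is λ = n·Σ(pᵢ − p̄)² / [p̄(1 − p̄)], and the critical value is 5.991.
- Rates .30/.45/.50: p̄ = .4167, Σ(pᵢ − p̄)² = .02167, p̄(1 − p̄) = .2431. At n = 110, λ = 9.81 and power is 80.7%. 80% needs 109 per arm.
- Rates .30/.40/.50: p̄ = .40, Σ(pᵢ − p̄)² = .0200, p̄(1 − p̄) = .24. At n = 110, λ = 9.17 and power is 77.9%. 80% needs 116 per arm.

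*(b) 75 versus 25 days alone, unpooled variance, two-sided alpha .025.* n = (z₁₋α/₂ + z₁₋β)²·[p₁(1 − p₁) + p₂(1 − p₂)] / (p₂ − p₁)² = (2.241 + 0.842)² × (.21 + .25) / .20² = 109.3, so 110.

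Both routes are standard. The article does not say which was used, or whether it was either of them.

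**Step 2. Power for each contrast in the primary objective.** Pooled-variance two-proportion formula, with d = p₂ − p₁, p̄ = (p₁ + p₂)/2, s₀ = √[2p̄(1 − p̄)] and s₁ = √[p₁(1 − p₁) + p₂(1 − p₂)]:

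- Power = Φ[(d√n − z·s₀)/s₁]
- Required n = [(z·s₀ + 0.842·s₁)/d]²

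At n = 110 and z = 1.960:

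| Contrast | d | s₀ | s₁ | (d√n − z·s₀)/s₁ | Power | n per arm for 80% |
|---|---|---|---|---|---|---|
| 50 vs 25 days, .45 vs .30 | .15 | .6847 | .6764 | 0.342 | 63.4% | 163 |
| 50 vs 25 days, .40 vs .30 | .10 | .6745 | .6708 | −0.407 | 34.2% | 356 |
| 75 vs 25 days, .50 vs .30 | .20 | .6928 | .6782 | 1.091 | 86.2% | 93 |

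**Step 3. Does another choice rescue 50 versus 25 days?**

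| Setting | .45 vs .30 | .40 vs .30 |
|---|---|---|
| 110 per arm, one-sided .05 | 74.6% | 46.4% |
| 110 per arm, two-sided .025 | 52.3% | 24.5% |
| 134 per arm (no loss), two-sided .05 | 72.0% | 40.3% |
| 134 per arm (no loss), one-sided .05 | 81.7% | 52.9% |
| 106 per arm (402 × .79 / 3), two-sided .05 | 61.8% | 33.1% |

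None of these reaches 80% at 110 per arm. The one entry above 80% needs the 45% rate, a one-sided .05 test and no loss at all, and the article itself assumes 21% loss.

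**Step 4. Multiplicity, conditional.** Suppose both contrasts were tested at unadjusted two-sided .05. With equal arms and a shared control the two statistics correlate at 0.5, and the chance of at least one false positive when neither regimen helps is about 9.1%.

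**The case against.** The article never claims 80% power for 50 versus 25 days. It claims it for detecting differences, and the Abstract speaks of differences among the three groups. On a global three-arm reading with 45%, the figure is right. This stands: a reader might infer an arithmetic error in the 110, and the documents do not support that.

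A reader might also infer that the 110 must come from the global test. That is not supported either, because route (b) in the working reaches it too, using only the two undisputed rates and an alpha split in two.

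The closer fit of the global test to .45 hints that .40 is a misprint. If so, the 34%, the 356 per arm and the 66% miss rate fall away. The document does not settle this, so those figures are conditional. The 63% would remain.

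It is also tempting to say that the two contrasts will be tested without any multiplicity allowance. The support for that is a general significance sentence placed at the end of the safety section. Such rules are commonly left to the full protocol or analysis plan, which are not shown, and route (b) is compatible with an allowance having been made. The 9% therefore describes a possible analysis and not one the article specifies.

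The objection does not remove the mismatch with the primary objective. A significant global test does not show which regimen beats 25 days, and a calculation for 75 versus 25 days says nothing about the 50-day arm.

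**Conclusion.** The point holds in this form: one design input is contradictory, and the 80% power has no named target and does not extend to one of the two comparisons in the primary objective. With 110 per arm and two-sided .05, 75 versus 25 days is adequately powered at 86%. For 50 versus 25 days, power is 63% at the 45% rate or 34% at the 40% rate. One-sided testing at .05 raises these to 75% and 46%, still under 80%.

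The results rest on the article's assumed rates, on 110 analysed patients per arm, and on an assumed sidedness. The contradiction in the 50-day rate needs no assumption, since it stands in a single phrase. The multiplicity remark is secondary and depends on how the contrasts will actually be tested.

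**What to change.** 1. Reconcile 45% and .40 for the 50-day arm, and correct whichever is wrong.
2. State the test, the comparison and the sidedness to which the 80% and the 110 refer. Only the sponsor knows this, and it should not be presumed to be the global test.
3. Report power for each extended regimen against 25 days. On two-sided .05 that is 86% for 75 days and 63% for 50 days (34% if .40 is the intended rate).
4. Say plainly that 50 versus 25 days does not have 80% power at 110 per arm, so a non-significant result there is not evidence of no effect.
5. Name the multiplicity rule for the two contrasts, or refer to the document that contains it. The choice is the sponsor's. A fixed sequence starting with 75 versus 25 days is one option, but it makes the 50-day claim depend on the arm whose adherence the Abstract doubts. By simulation, it also lowers the chance of confirming a 45% rate from 63% to about 59%.

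The cost is a few restated figures and sentences. No patients are added and the design does not change. The price is a less favourable stated power for the 50-day arm.

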## Methods

### Trial Design

Phase IV randomized, open-label, controlled, parallel, multicenter clinical trial in patients who are candidates for smoking cessation to demonstrate the superiority of maintenance therapy with cytisinicline compared to the standard regimen.

The trial was designed according to the standardized guide for interventional trial protocols, SPIRIT (Standard Protocol Items: Recommendations for Interventional Trials statement [Multimedia Appendix 2]). A total of 402 patients from 10 smoking cessation units in Spain will be randomized. Recruitment will last for one year, with a follow-up of 52 weeks per patient recruited. Candidate patients who sign the informed consent form will be randomized to 3 possible arms in a ratio of 1:1:1.

Arm A: control group. Participants randomized to this group will be treated with cytisinicline as stated in the data sheet. They must remain smoke-free from day 5 of treatment.

Arm B: maintained therapy 1. Following the standard regimen, these patients will maintain treatment for an additional 25 days at a dose of 1.5 mg twice daily.

Arm C: maintained therapy 2. Following the standard regimen, these patients will maintain treatment for an additional 50 days at a dose of 1.5 mg twice daily (see Table 1).

At the end of the treatments, participants will continue in the follow-up phase, without treatment, until completing 52 weeks in the study (see Figure 1).

**Table 1 table1:** Dosage guidelines in each of the 3 treatment arms.

Days of treatment		Recommended dosage	Maximum daily dose	Recommendations	

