### Study Population

This study will be conducted in the Smoking Cessation Units (SCU) of 10 Spanish hospitals with different levels of complexity of care that provide care to active smokers who wish to quit smoking. An SCU is defined as a health care service integrated within a health area that promotes, coordinates, and implements actions to prevent and treat smoking in that area, in direct collaboration with the area’s health care services. The main objectives of SCUs are clinical care, education, research, and management [26]. The SCUs are accredited by the Spanish Society of Pneumology and Thoracic Surgery and by a public agency. Their geographical distribution is representative of the Spanish population (see Table 2).

**Table 2 table2:** Smoking Cessation Units (SCU) of 10 Spanish hospitals, with different levels of complexity of care, that provide care to active smokers who wish to quit smoking.

Recruitment centers	Estimated number of patients
University Clinical Hospital of Santiago de Compostela	42
Galdakao Hospital, Bilbao	30
San Pedro de Alcántara Hospital, Cáceres	60
San Carlos Clinical Hospital, Madrid	90
October 12 University Hospital, Madrid	40
Clinic Hospital, Barcelona	30
Alcorcón Foundation Hospital, Madrid	30
Virgen de la Macarena University Hospital, Sevilla	40
University Clinical Hospital of Valencia	20
Virgen de la Victoria Hospital, Málaga	20

The sample size of the Cytisinicline Treatment for Smoking Cessation–Long-term Study (CITISILONG) trial (N=402) is based on a minimum number of patients for each of the treatment arms. The sample size calculation is given in the Statistical Analysis section of the Methods section.

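### With 21% of 402 patients lost, about 106 per arm remain, not the 110 that the sample size calculation requires

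*Protocol article*

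**What the plan says.** Sample Size Determination in the Protocol article gives all the figures. The aim is put as "To obtain 80% power (pow=0.80") "to detect differences at a 5% significance level (α=.05"), for which "110 patients would need to be included in each arm". The next sentence reads "A loss rate of 21% is assumed, giving a final sample size of 402 patients (N=402").

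Trial Design has patients "randomized to 3 possible arms in a ratio of 1:1:1", so 402 means 134 per arm. Study Population says that the size "is based on a minimum number of patients for each of the treatment arms", and the ten site targets in Table 2 add up to 402. Population of Analysis places both efficacy and safety in the clinically evaluable patients. The article prints neither the inflation formula nor the test behind the 110.

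**The concern.** An allowance for losses exists so that the required number is still there after the losses have occurred. A loss rate is a share of the patients enrolled, so the required number has to be divided by one minus that rate. Adding 21% to the required number gives a smaller total, which falls short once 21% of that total is lost.

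What is at stake is the claim that readers will take from this paragraph: 80% power with a 21% loss already allowed for. If the printed size does not leave 110 per arm, that claim is not true on the plan's own figures.

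**Working it through.** **Inputs**, from Sample Size Determination unless noted: 110 required per arm; loss 21%; final N 402; three equal arms (Trial Design); α 0.05; power 80%; assumed rates 30% (25 days), 45% in words but .40 in brackets (50 days), 50% (75 days).

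**1. Reproducing 402.**
- Multiplying: 110 × 1.21 = 133.1, rounded up to 134 per arm; 3 × 134 = 402. Exact match.
- Dividing: 110 / 0.79 = 139.2, rounded up to 140 per arm; 3 × 140 = 420. Rounded on the total: 330 / 0.79 = 417.7, so 418. Neither is 402.

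**2. What 402 leaves**, with losses spread evenly over the arms.
- Total: 402 × 0.79 = 317.6, against 330 required.
- Per arm: 134 × 0.79 = 105.9, against 110.
- Shortfall: about 4 evaluable patients per arm, 12 in total. In enrolment terms the gap is 418 − 402 = 16 or 420 − 402 = 18.

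This step uses only the printed figures and holds whatever formula produced 402.

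**3. The loss that 402 does cover.** 1 − 330/402 = 17.9%.

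**4. Effect on power.** The test is not stated, so one has to be assumed. For a three-group chi-square test (2 df) with per-arm size n, the noncentrality is n × Σ(pᵢ − p̄)² / [p̄(1 − p̄)].
- At 30/45/50%: p̄ = 0.4167, Σ(pᵢ − p̄)² = 0.02167, p̄(1 − p̄) = 0.2431, ratio 0.0891.
- 80% power needs 109 per arm, which fits the printed 110 closely and leaves almost no slack.
- n = 110: noncentrality 9.81, power 80.7%.
- n = 106: noncentrality 9.45, power 79.2%.

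A second design also fits 110: 30% against 50%, two-sided α 0.025, unpooled variance. Power is Φ(0.20 / √(0.46/n) − 2.241).
- n = 110: Φ(3.093 − 2.241) = 80.3%.
- n = 106: Φ(3.036 − 2.241) = 78.7%.

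Under either design the cost is about 1.5 percentage points.

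**The case against.** Four points can be made for the plan.

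**The loss of power is trivial.** About 1.5 points is less than the uncertainty in assumed rates that rest on clinical experience. This stands, and it limits the weight of the point. It does not make the printed figures agree.

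**The multiplication by 1.21 is inferred.** It appears nowhere in the article, and it matches only when rounding up per arm, since 330 × 1.21 = 399.3. The site targets also sum to 402, so the article does not show which number came first. This stands too: the cause is probable, not established. The shortfall does not depend on it.

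**Lost patients may not leave the analysis.** The evaluable population is not defined. If all 402 were analysed with missing counted as smoking, there would be no shortfall; at 134 per arm the three-group test at 30/45/50% has about 88% power, provided those rates already count missing that way. No such rule is stated, however, and under it a loss inflation would have no purpose, so the paragraph would still need rewording.

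**A reader might infer that the loss allowance leaves the trial badly underpowered**, for example from a 50- versus 25-day power of 62% or 33% at 106 per arm. The documents do not support that. At two-sided 0.05 and the full 110 per arm, those powers are already 63.4% (30% vs 45%) and 34.2% (30% vs 40%); at 106 they are 61.8% and 33.1%. Likewise the three-group power at 30/40/50% is 77.9% at 110 and 76.2% at 106. The low values come from the assumed rates, the base calculation and the conflict between 45% and .40. Those are separate matters; the loss allowance costs one to two points.

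**Conclusion.** The point holds as an internal inconsistency with a modest consequence. On the article's own numbers, 402 patients with a 21% loss leave about 106 per arm and not 110, and nothing elsewhere in the article repairs this: Trial Design and the site table both confirm 402 as the working number.

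The arithmetic rests only on printed figures and equal loss across arms. The harm to power rests on lost patients leaving the analysis, which is the natural but not the certain reading of the evaluable population. The power of 79.2% further assumes the three-group test and the 45% reading of the 50-day rate. It should not be quoted as the trial's power until the authors confirm both.

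**What to change.** No further enrolment is needed. In Sample Size Determination, do one of the following.

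- Say that 402 patients with a 21% loss leave about 106 evaluable per arm, and give the power at 106 for the test and rates actually used to obtain 110. That is about 79% if it was the three-group test at 30/45/50%.
- Say that 402 protects 110 per arm only up to a loss of 17.9%. This should be worded as a limit and not as a new expected loss rate, because nothing in the article supports 17.9% as an expectation.
- If all randomised patients are to be analysed with missing counted as smoking, say so, drop the loss inflation, and state the power at 134 per arm on abstinence rates defined that way.

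Whichever is chosen, name the test behind the 110. The cost is a few restated figures and, under the first option, a power slightly below the 80% target if either design shown above was the one used.
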